## Abstract

**Background:**

Repetitive transcranial magnetic stimulation (rTMS) and median nerve electrical stimulation (MNES) are two non-invasive neuromodulation techniques that have demonstrated potential in facilitating the recovery of consciousness in patients with impaired consciousness. However, existing studies on awakening interventions for patients with prolonged disorders of consciousness (pDoC) following intracerebral hemorrhage remains limited. In particular, systematic comparisons of the efficacy of rTMS versus MNES in this specific patient population are lacking.

**Methods:**

This is a single-center randomized controlled trial in which 45 patients will be randomly assigned to the control group, rTMS group and MNES group. The intervention period will lasts 4 weeks. All patients underwent multimodal assessments before and at the end of treatment, which were used to comprehensively evaluate their recovery of consciousness and changes in brain function. The assessments includes the Coma Recovery Scale, electroencephalogram, event-related potentials (P300 and mismatched negative) and functional near-infrared spectroscopy.

**Discussion:**

This study represents the first systematic comparison of the efficacy between rTMS and MNES in patients with pDoC following intracerebral hemorrhage. The objective is to employ multimodal assessment techniques to provide clinical references into the individualized application of these neuromodulation therapies.

**Clinical trial registration:**

https://www.chictr.org.cn/, identifier ChiCTR2400082022.

## Introduction

Prolonged disorders of consciousness (pDoC) encompass a spectrum of conditions caused by severe brain injury, including unresponsive wakefulness syndrome and minimally conscious state (1). These patients are in a prolonged state of absent or severely limited consciousness, which seriously affects their quality of life (2). Due to their inability to live independently, they impose a huge medical and economic burden on society (3). Most of the existing studies have focused on traumatic brain injury or have not specified the etiology, while relatively few studies have addressed pDoC resulting from intracerebral hemorrhage (4). pDoC after intracerebral hemorrhage often carry a poor prognosis (5), and it highlights the need for research and treatment development for this specific etiology (6).

Non-invasive neuromodulation techniques have shown some potential in improving the prognosis of pDoC patients. Repetitive transcranial magnetic stimulation (rTMS) works by generating rapidly changing magnetic fields in specific regions of the cerebral cortex, which induce neuronal depolarization. This process modulates neuronal excitability and synaptic plasticity, aiming to promote arousal in patients with pDoC (7). Wan et al. (2) showed that the application of high-frequency rTMS significantly improved coma recovery scale-revised (CRS-R) scores, and provided further evidence through event-related potentials (ERPs). Bai et al. (8) confirmed that rTMS improved cortical excitability and cortical connectivity in pDoC patients by electroencephalogram (EEG) and TMS-EEG, explaining the potential mechanism of rTMS in pDoC wakefulness promotion.

Median nerve electrical stimulation (MNES) is a peripheral neuromodulation technique, which activates the ascending reticular activating system (ARAS) by enhancing sensory afferents through direct stimulation of the median nerve (9). In turn, it improves the neural activity and functional connectivity of the frontal lobe and other cortical areas related to consciousness, and promotes the recovery of consciousness (10). Most studies on MNES in promoting awakening have focused on coma patients (11). Xiong et al. (12) reported that MNES significantly enhanced the cortical brain activity with pDoC, and this effect was confirmed through the EEG. It suggests the potential value of MNES in boosting consciousness levels in pDoC.

Functional near-infrared spectroscopy (fNIRS) is a non-invasive brain imaging technique that has gained traction in recent years. Compared to other imaging techniques such as functional magnetic resonance imaging and positron emission tomography, fNIRS exhibits significant advantages in a number of ways. Its high temporal resolution allows for rapid acquisition of cortical oxygenation data (13). fNIRS is mobile and flexible enough to be used at the bedside or in dynamic environments. In addition, fNIRS is less affected by motion artifacts and still obtain more accurate brain data with patients’ slight movements (14). Si et al. (15) demonstrated that fNIRS was able to effectively differentiate changes in cortical blood oxygenation in different states of consciousness, validating the potential application of fNIRS in pDoC studies.

This study aims to systematically compare the efficacy of rTMS and MNES in pDoC patients after intracerebral hemorrhage by multimodal assessments. This research offers new perspectives on the distinct mechanisms of central and peripheral neuromodulation techniques and their clinical applications. The findings are expected to inform the optimization of future treatment plans and the development of personalized intervention strategies.

## Methods

### Study design

This study is a single-center, randomized controlled trial (Figure 1). The study complies with the Declaration of Helsinki and was approved by the Ethics Committee of the Fifth Affiliated Hospital of Zhengzhou University (Approval No. KY2023093).

**Figure 1 fig1:**
[figure not shown]
The study design. rTMS repetitive transcranial magnetic stimulation; MNS, median nerve electrical stimulation; CRS-R, coma recovery scale-revised; ERPs, event-related potentials; FNIRS, functional near-infrared spectroscopy.

### Participants

All patients will be recruited from the Department of Rehabilitation Medicine, The Fifth Affiliated Hospital of Zhengzhou University, China. The study lasts from December 2023 to December 2024.

Inclusion criteria: (1) Diagnosed with hemorrhagic stroke, and assessed as minimally conscious state (MCS) or unresponsive wakefulness syndrome (UWS) according to the CRS-R assessment (16); (2) Aged between 18 and 75 years; (3) Normal brainstem auditory evoked potentials on at least one side; (4) No history of craniotomy involving the left dorsolateral prefrontal cortex; (5) The guardian signed an informed consent.

Exclusion criteria: (1) Intracranial metal implants or large cranial defects; (2) Unstable vital signs; (3) Seizures within the past 4 weeks; (4) Concurrently receiving other neuromodulatory treatments; and (5) Participants who withdrew from the study midway.

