### Sample size

Sample size estimation was estimated using G-Power software. The CRS-R effect size was based on similar studies from the literature (17). The effect size was taken as 0.62, *α* = 0.05, and efficacy power (1-*β*) = 0.95. Considering a dropout rate of 20%, the total sample size was calculated to be 45 cases. The results of the sample size calculation provided a solid foundation to ensure that the effect of the intervention could be effectively detected in this study.

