### Randomization and blinding

The randomized sequence will be generated by SPSS 26.0 software. Patients will be divided into 3 groups according to the order of enrollment in a 1:1:1 manner: 15 cases in the conventional group, 15 cases in the rTMS group, and 15 cases in the MNES group. The results of the patient grouping will be sealed in opaque envelopes to ensure concealment of the allocation, and these envelopes will be kept by a special person and revealed only at the time of allocation. For objectivity of the study, patients, assessors and data analysts will all be blinded. It ensures that potential bias is avoided during evaluation and data processing.

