### Statistical analysis

Data analysis is conducted using SPSS 26.0 software. Normality and homogeneity of variance tests are first performed on the measurement data. Normally distributed data are expressed as mean ± standard deviation. One-way analysis of variance is used for between-group comparisons, and paired t-tests are used for within-group comparisons. For data that do not conform to normal distribution, the median and interquartile range are expressed, and Kruskal-Wallis test is used for between-group comparison. Count data were analyzed for variability by chi-square test. For rank data, Mann–Whitney U test and Wilcoxon signed rank test are used. The confidence interval for all statistical results is 95%, with *p* < 0.05 as the criterion for statistically significant differences.

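### Exclusion criterion (5) is a post-randomisation event; applied as written, it removes randomised patients from the trial

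*Protocol article*

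**What the plan says.** The Participants section of the protocol article gives five exclusion criteria. The first four (implants or large cranial defects, unstable vital signs, recent seizures, other neuromodulation) can be judged before entry. The fifth is "5) Participants who withdrew from the study midway".

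The Sample size section expects losses: "Considering a dropout rate of 20%, the total sample size was calculated to be 45 cases". Under Randomization and blinding, "Patients will be divided into 3 groups according to the order of enrollment in a 1:1:1 manner", with 15 patients per arm and the allocation revealed from sealed envelopes only at assignment.

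The Statistical analysis section names tests ("One-way analysis of variance is used for between-group comparisons, and paired t-tests are used for within-group comparisons") but says nothing that would keep a withdrawn patient in the comparison. The Treatment section says that cases of adverse reactions will be recorded during the experiment and does not limit this to patients who finish.

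**The concern.** Randomisation makes the three arms comparable at the moment of allocation. A rule that then removes patients for something that happens afterwards can undo this, because those who remain are selected by events that may be linked to treatment or to recovery. An eligibility list is the wrong place for such a rule: nobody can apply criterion (5) at screening, so it can work only as an instruction to take enrolled patients out.

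This is a rule that the article states, not a gap left to a fuller document. If an analysis plan that is not shown keeps all randomised patients, it conflicts with criterion (5), and one of the two texts must change. At stake is who counts in every between-arm comparison of a 45-patient trial.

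**Working it through.** **Step 1. When can each criterion be judged?** Criteria (1) to (4) are known at screening. Criterion (5) requires the patient to be in the study already, and patients are allocated by order of enrolment. A patient who meets criterion (5) will therefore ordinarily have been randomised.

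**Step 2. How many patients?** Inputs: 45 randomised, 15 per arm, 20% dropout (Sample size; Randomization and blinding).
- Removed: 0.20 × 45 = 9, or 0.20 × 15 = 3 per arm if spread evenly.
- Remaining: 45 − 9 = 36, and 36 / 0.80 = 45, so the allowance read this way is consistent with the stated total.

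Whether 45 follows from the stated effect size and power is a separate question. The test and the type of effect size are not given, so the total can be neither confirmed nor called wrong. One-way ANOVA with 0.62 taken as Cohen's f, α = 0.05 and power 0.95 needs 44 patients, or 45 in equal arms, before any dropout. A two-sided paired t-test with d = 0.62 needs 36, and 36 / 0.80 = 45. Nothing below depends on this.

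**Step 3. What could removal do?** The document gives no reasons for withdrawal, so this step uses assumptions. Outcomes are N(0,1) in all arms (no true effect), with 15 per arm, about 20% lost per arm, and one-way ANOVA at 0.05 on those who remain. Bias is the mean of the affected arm minus the mean of the others, in SD units. Soft loss means that the chance of leaving rises as the outcome worsens, through a logistic curve with slope 1 to 2 per SD, set to average about 20%.

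| Pattern of loss | Bias | Type I error |
|---|---|---|
| Random in all arms | about 0 | 5% |
| Soft outcome-related, equal in all arms | about 0 | 5% |
| Soft outcome-related in one arm, random in the others | about 0.18 to 0.27 SD | 7 to 9% |
| Three worst lost in one arm, random in the others | about 0.33 SD | 14% |
| Three worst lost in every arm | about 0 | about 11% |

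In the third row, the low end belongs to slope 1 and the high end to slope 2.

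**Step 4. Check of the fourth row by hand.** The three lowest of 15 standard normal values average about −1.31. All 15 sum to zero on average, so the other 12 sum to 3 × 1.31 = 3.93 and average 3.93 / 12 = 0.33 SD, as simulated.

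**Step 5. Reading the 14%.** The last row has no bias, yet its error rate is about 11%. Cutting off the low tail shrinks the within-arm variance that ANOVA uses as its yardstick. The 14% therefore mixes bias between arms with this variance effect and should not be read as bias alone.

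**The case against.** The strongest reply is that this is a drafting slip in a condensed article and that the analysis set belongs in a plan that is not shown. That limits what can be concluded, but not the point itself: the printed criterion is still wrong and would contradict any such plan. A patient who withdrew between consent and allocation could be left out harmlessly, but the criterion is not confined to that case.

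Several stronger readings are tempting and are not supported:
- *The trial will analyse completers only.* A reader might infer this, but the article does not say so. It is what follows if criterion (5) is applied as written.
- *Every patient who stops is removed, including those who die or are transferred.* The criterion concerns withdrawal from the study. It does not equate this with stopping stimulation, death or transfer.
- *Nine patients will be removed.* The 20% is a planning allowance, so 9 is the figure if that allowance is realised through withdrawals.
- *A patient who stops because of a seizure disappears from the safety results.* The Treatment section records adverse reactions in patients without limiting this to completers. Whether withdrawn patients are counted in the final tally is not stated either way.
- *Withdrawal will differ by arm.* Each active arm also receives the other sham, the control arm receives both shams, patients and assessors are to be blinded, and treatment lasts four weeks. Loss related to outcome is plausible; a difference between arms is an assumption. Hence the zero-bias rows belong in the range.

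**Conclusion.** The point holds in a limited form. Criterion (5) is a post-randomisation event printed as an eligibility rule, and nothing in the article keeps the affected patients in the analysis. That part rests on the text alone and is firm.

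The consequence is conditional. Up to 9 of 45 randomised patients could be removed at the article's own dropout rate. Under the null scenarios above, the effect runs from no bias and 5% type I error to about 0.33 SD and 14%, with 0.18 to 0.27 SD and 7 to 9% for softer one-arm loss. These figures rest on assumed normal outcomes and assumed reasons for leaving. They show what the rule could do and do not predict the direction or size of bias in this trial.

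**What to change.** - Delete criterion (5) from the eligibility list and describe withdrawal as a post-randomisation event.
- State that all randomised patients are analysed in their assigned arm.
- Seek the end-of-treatment CRS-R from patients who stop stimulation, where consent allows.
- State that the adverse reactions recorded under Treatment are counted for withdrawn patients too.
- Name a method for missing end-of-treatment scores and add a sensitivity analysis for outcome-related loss. The sensitivity analysis is needed because imputation that assumes data missing at random would not fully remove loss that depends on the unseen outcome, which is the loss simulated above.
- Keep a completer analysis, if wanted, as supportive only.

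The cost is a few lines of text and some effort to assess patients who stop early. The planned total of 45 does not change.

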### Sample size

Sample size estimation was estimated using G-Power software. The CRS-R effect size was based on similar studies from the literature (17). The effect size was taken as 0.62, *α* = 0.05, and efficacy power (1-*β*) = 0.95. Considering a dropout rate of 20%, the total sample size was calculated to be 45 cases. The results of the sample size calculation provided a solid foundation to ensure that the effect of the intervention could be effectively detected in this study.

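### For the planned three-arm ANOVA, 95% power, 20% dropout and 45 patients cannot all hold: if 0.62 is Cohen's f, power after dropout is about 90%

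*Protocol article*

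**What the plan says.** The Sample size section of the protocol article reports a G*Power calculation with a CRS-R effect size drawn from similar literature: "The effect size was taken as 0.62". It sets alpha at 0.05 and power at 0.95, and then states: "Considering a dropout rate of 20%, the total sample size was calculated to be 45 cases". It names neither the G*Power routine nor the effect-size metric. It ends by presenting the result as firm assurance that the intervention effect can be detected.

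The Randomization and blinding section divides the total equally: "15 cases in the conventional group, 15 cases in the rTMS group, and 15 cases in the MNES group".

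The Statistical analysis section gives the test for normally distributed data: "One-way analysis of variance is used for between-group comparisons". Paired t-tests are reserved for change within a group. No repeated-measures model is listed.

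**The concern.** The text presents 45 as a total that already allows for losing one patient in five, and 0.95 as the power that remains. If 45 is instead what the planned test needs with complete data, the stated power does not apply to the trial that the protocol expects to complete. The stated aim is to compare rTMS with MNES, and a control arm is included, so the between-group test is the one whose power matters. Overstated power makes a non-significant result look like stronger evidence of no difference than it is. The unstated metric adds to this, because 0.62 as Cohen's f and 0.62 as a two-group d describe effects of very different size.

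**Working it through.** **Inputs**
- Effect size 0.62, alpha 0.05, power 0.95, dropout 20%, total 45 (Sample size).
- Three arms, 15 each (Randomization and blinding).
- One-way ANOVA between groups (Statistical analysis).
- Assumption: 0.62 is Cohen's f, which is G*Power's metric for one-way ANOVA. The document does not say so.

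**Formula.** The omnibus F test has k − 1 = 2 and N − 3 degrees of freedom and noncentrality λ = N × f², with f² = 0.62² = 0.3844. Power is the probability that this noncentral F exceeds the 5% critical value of the central F.

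**Step 1: the plan's own figure.**

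| N analysed | λ = N × 0.3844 | Power |
|---|---|---|
| 36 | 13.84 | 0.899 |
| 42 | 16.14 | 0.943 |
| 45 | 17.30 | 0.958 |

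The smallest equal-arm total reaching 0.95 is 45. So 45 is reproduced, but as the requirement before any dropout.

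**Step 2: add the dropout.** 45/(1 − 0.20) = 56.25, rounded up to 57 (19 per arm). The cruder 45 × 1.2 gives 54. Neither is 45.

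**Step 3: power of the trial as sized.** 45 × 0.80 = 36 analysed, 12 per arm. Power is 0.899, so the type II error is 10% where the plan states 5%. For 95% power at 36, f would have to be 0.69.

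**Step 4: what f = 0.62 means.** With the three means evenly spaced, the extreme arms differ by 0.62 × √6 = 1.52 SD. With one arm apart from two equal arms, they differ by 0.62 × 3/√2 = 1.32 SD.

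**Step 5: if 0.62 is a standardised difference d.**

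| Conversion to f | f | Power at 36 | Power at 45 |
|---|---|---|---|
| Largest gap d, even spacing: d/√6 | 0.253 | 0.24 | 0.29 |
| Largest gap d, one arm apart: d√2/3 | 0.292 | 0.30 | 0.38 |
| Two-group conversion: d/2 | 0.31 | 0.34 | 0.42 |

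**Step 6: other routes to 45.**
- Repeated-measures ANOVA, between factors, with f = 0.62, 2 measurements and assumed correlation ρ: λ = N × f² × 2/(1 + ρ). At ρ = 0.5, power is 0.948 at 33 and 0.965 at 36, so 36 are needed and 36/0.8 = 45. The result depends on ρ: after dropout, ρ = 0.3 gives 38 and ρ = 0.7 gives 49.
- Two-sided paired t-test with dz = 0.62: power is 0.945 with 35 pairs and 0.951 with 36, so again 36/0.8 = 45. The plan uses this test within each arm, where 12 completers give power of 0.50.

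**The case against.** A reader might infer that dropout was simply forgotten. The document does not support that. It says that dropout was considered, it does not name the routine, and Step 6 shows two calculations in which 45 is a correctly inflated 36. One of them, the paired t-test, is a test that the protocol does plan. The fault may therefore be a mismatch between the test that was powered and the test that will compare the arms. This part of the objection stands, and the cause has to be left open.

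It can also be said that a journal article may leave the routine and the metric to the full protocol. Their absence alone would indeed be no finding. What remains is that the inputs and the total are both stated, and that they do not agree for the only parametric between-group test named.

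Neither alternative route restores the claim. The repeated-measures between-factors routine tests the average of the baseline and post-treatment scores, which is not a planned analysis. The paired test needs 36 pairs in one comparison, does not compare arms, and has 12 pairs per arm after dropout.

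Finally, 90% power is conventionally adequate. That is correct, and it limits the severity.

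**Conclusion.** The point holds in conditional form. For the planned three-arm one-way ANOVA, the stated power, dropout and total are mutually inconsistent. If 0.62 is Cohen's f, power after the stated 20% loss is 0.90, and 0.95 is reached only if essentially all 45 patients are analysed. This is a moderate error: about five percentage points of power, with a remaining level that most would accept if an effect that large is real.

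A stronger reading, that the trial is badly underpowered, would follow if 0.62 were a two-group d (power about 0.24 to 0.34 at 36). The document does not establish that, and the cited source is not available here, so these figures show why the metric must be stated. They do not raise the severity.

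The figures assume equal arms after dropout and the omnibus F test under its usual assumptions.

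**What to change.** No patients need to be added. In the Sample size section:

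1. Check in the cited source whether 0.62 is f or d, and state the metric.
2. Name the test and the G*Power routine used. If it was not the one-way ANOVA, recompute for the one-way ANOVA.
3. State that 45 are randomised, that 36 are expected to be analysed after 20% loss, and the ANOVA power at 36. If f = 0.62 is confirmed, that is about 0.90, with 0.95 only if no patient is lost. If 0.62 is a d, the power must be recomputed and will be far lower.
4. Give the between-arm CRS-R difference that the effect size implies, so that a reader can judge whether it is plausible.
5. Qualify the closing statement that the calculation ensures the effect can be detected.

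The cost is a look at the source, one rerun of the calculation and a few sentences. The reported power becomes less favourable. Keeping 95% after dropout would instead mean 57 patients, which this fix does not ask for.

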### Randomization and blinding

The randomized sequence will be generated by SPSS 26.0 software. Patients will be divided into 3 groups according to the order of enrollment in a 1:1:1 manner: 15 cases in the conventional group, 15 cases in the rTMS group, and 15 cases in the MNES group. The results of the patient grouping will be sealed in opaque envelopes to ensure concealment of the allocation, and these envelopes will be kept by a special person and revealed only at the time of allocation. For objectivity of the study, patients, assessors and data analysts will all be blinded. It ensures that potential bias is avoided during evaluation and data processing.

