### Outcomes

#### CRS-R

The CRS-R is one of the most accurate and recommended behavioral scales for the evaluation of consciousness in pDoC. It assesses the state of consciousness from six different perspectives: auditory, visual, motor, verbal, communication, and arousal (18). CRS-R’s unique multi-dimensional design enables it to acutely reflect patients’ responses in different situations. In particular, it shows high sensitivity in distinguishing the difference in level of consciousness between MCS and UWS patients. The evaluator assesses the patient five times within 7 days and selects the highest score to be used for classification. Based on the scores, the patients’ level of consciousness can be categorized as UWS, MCS-, MCS+, and emergence from MCS (19).

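### UWS and MCS patients are mixed, but the article describes neither stratified allocation nor an analysis adjusted for class or baseline CRS-R, which costs precision with 15 per arm

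*Protocol article*

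**What the plan says.** The inclusion criteria (Participants) admit patients "assessed as minimally conscious state (MCS) or unresponsive wakefulness syndrome (UWS) according to the CRS-R assessment". The CRS-R section says of the scale that "it shows high sensitivity in distinguishing the difference in level of consciousness between MCS and UWS patients", and uses its scores to place patients in UWS, MCS-, MCS+ or emergence from MCS.

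On how the list is made, Randomization and blinding says only that "The randomized sequence will be generated by SPSS 26.0 software". The allocation rule that it gives is "Patients will be divided into 3 groups according to the order of enrollment in a 1:1:1 manner", and each arm is planned to hold 15 patients. The section goes on to concealment and blinding. It names no stratification factor, block or minimisation.

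Statistical analysis compares arms by one-way ANOVA or, for non-normal data, Kruskal-Wallis. It uses chi-square for counts and Mann-Whitney and Wilcoxon tests for ranked data. No baseline value or diagnostic class enters any of these comparisons. The section does not say whether end-of-treatment scores or changes are compared.

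**The concern.** Class is a banding of the CRS-R, so an imbalance in class is an imbalance in the baseline level of the behavioural outcome. The Discussion also ties EEG grade and P300 to the CRS-R and MMN to the level of consciousness, and the fNIRS task is driven by commands. One chance imbalance could therefore push several outcomes in the same direction.

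The Introduction gives the comparison of rTMS with MNES as the aim, and each of those arms has 15 patients. As described, nothing controls class at allocation and nothing adjusts for it in the analysis. At stake are the precision of the main contrast and the reader's ability to interpret it if one active arm happens to hold several more MCS patients.

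**Working it through.** **Inputs.** From Randomization and blinding: three arms of 15, 3 × 15 = 45. Assumed, because the article does not give them: a UWS share of 20% to 80%; a UWS-MCS difference in end-of-treatment CRS-R of 4 to 8 points; a within-class SD of 3 to 4 points.

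**The plan's own figure.** "Considering a dropout rate of 20%, the total sample size was calculated to be 45 cases". The 45 is reproduced, for example, by a repeated-measures ANOVA (between factors, 3 groups, 2 measurements, assumed correlation 0.5, f = 0.62, power 0.95): 36 before dropout, and 36 / 0.8 = 45. The article does not name the test behind the calculation. Only the arm size of 15 matters below.

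**Chance imbalance.** With K UWS patients among 45 and three arms of 15 filled at random, the counts (a, b, c) have probability C(15,a) × C(15,b) × C(15,c) / C(45,K), with a + b + c = K. Summing over the relevant cells gives:

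| UWS patients (share) | rTMS-MNES gap ≥ 3 (20 points) | gap ≥ 4 (27 points) | gap ≥ 5 (33 points) | some pair of arms, gap ≥ 4 |
|---|---|---|---|---|
| 9 or 36 (20% or 80%) | 0.26 | 0.11 | 0.04 | 0.25 |
| 15 or 30 (33% or 67%) | 0.34 | 0.18 | 0.08 | 0.36 |
| 18 or 27 (40% or 60%) | 0.36 | 0.20 | 0.10 | 0.39 |
| 22 or 23 (about 50%) | 0.37 | 0.21 | 0.10 | 0.42 |

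The expected absolute rTMS-MNES gap is 1.75 to 2.19 patients.

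**Effect on one trial.** A gap of 4 patients shifts the unadjusted difference in end-of-treatment means by (4/15) × class gap: 1.1 points for a class gap of 4, 1.6 for 6 and 2.1 for 8.

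**Loss of precision.** With UWS share p, class gap D and within-class SD s, the total variance divided by the within-class variance is 1 + p(1 - p)D²/s².

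- p = 0.5, D = 4, s = 4: 1 + 0.25 × 16/16 = 1.25.
- p = 0.5, D = 8, s = 3: 1 + 0.25 × 64/9 = 2.78.

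The unadjusted standard error is thus √1.25 = 1.12 to √2.78 = 1.67 times the within-class one. At a 20% or 80% share the variance ratio is lower, 1.16 to 2.14 (0.16 in place of 0.25).

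**Type I error.** Simulation with no treatment effect, 22 UWS of 45, random allocation, an unadjusted t test of 15 against 15, and the gaps and SDs above (40,000 draws each) gives rejection rates of 0.049 to 0.052. The overall rate is therefore the nominal 5%. Given an imbalanced split of 9 against 5 UWS patients, the rate is 0.07 to 0.09.

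**After the fix.** Within a class, permuted blocks of 3 hold the rTMS-MNES gap to at most 1 patient, and blocks of 6 to at most 2.

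**The case against.** Four objections have weight.

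1. The article is condensed and never says that allocation is unstratified. Taking patients in order of enrolment is also compatible with separate lists per class. This stands as a caution. A single sequence applied in order of enrolment is the natural reading, but it is an inference. The analysis half of the point does not depend on it, because the tests are named and contain no covariate.

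2. A reader might infer that a large imbalance between rTMS and MNES is likely. The numbers do not support that. A gap of 4 or more has at most a 21% chance, and a gap of 5 or more at most 10%. Even for some pair of arms, a gap of 4 or more stays below one half.

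3. A reader might infer that imbalance biases the trial or produces excess false positives. It does neither on average. The standard error of the unadjusted test already includes the variation between classes, and the simulated rejection rate is 5%. Nor is it true that ranked and categorical outcomes cannot be adjusted later: stratified rank tests, Cochran-Mantel-Haenszel tests and ordinal regression exist. The article simply does not plan them.

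4. The UWS/MCS mix, the class gap and the within-class SD are not in the article, and it does not call class the main prognostic factor. If changes rather than end scores are compared, a stable difference in level cancels. The shift of 1.1 to 2.1 points then does not apply, and only a difference in course between the classes would matter. This also stands, which is why ranges are shown.

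A single unstratified list would be a valid design. The objections reduce the size of the point but do not remove it: the trial already collects a strong baseline correlate of its outcomes and, as described, uses it at neither stage.

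**Conclusion.** The point holds as a cheap improvement and is not a fatal flaw. Following the article as written leaves class and baseline CRS-R uncontrolled at the between-arm comparison and, on the natural reading, at allocation too. The chance that rTMS and MNES differ by at least 4 UWS patients is about 1 in 5 (11% to 21% for a UWS share of 20% to 80%), and 25% to 42% for some pair of arms.

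The cost is precision and interpretability. For end-of-treatment CRS-R, the outcome variance is about 1.25 to 2.8 times the within-class variance with half the patients UWS, a class gap of 4 to 8 points and a within-class SD of 3 to 4. A single trial with a 4-patient gap would be hard to read. The probabilities rest on the stated arm sizes and the assumed mix; the variance ratio rests entirely on the assumed gap, SD and mix.

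**What to change.** In the between-arm comparison, adjust CRS-R and the other continuous outcomes for their baseline value by ANCOVA. For EEG grade and categorical outcomes, use class-stratified rank tests, Cochran-Mantel-Haenszel tests or ordinal regression with class as a term. This remains possible whatever the state of recruitment, provided it is fixed before the data are unblinded. The Participants section gives a study period of December 2023 to December 2024, so allocation may already be complete.

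If allocation is still open, also generate separate permuted-block lists for UWS and MCS, classed at the pre-treatment CRS-R, with blocks of 3 and 6, and include the stratum in the analysis. If the full protocol already stratifies, say so in the article.

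Cost: slightly more analysis and, for the allocation part, a second list and envelope set. No extra patients or assessments are needed. Arm sizes may end between 13 and 17 instead of exactly 15. For example, incomplete last blocks of six can leave 8, 8, 6 among 22 UWS patients and 9, 7, 7 among 23 MCS patients, which totals 17, 15 and 13.
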